### Patient and public involvement

The study proposal was presented to the Public Involvement in Research Group at Sheffield Hallam University who provided feedback on the study plan and recommendations about how to improve the participant experience during the study. In addition, two patient and public focus groups will be held for the project which will include patients, service users, and/or their carers and members of the public. The first has taken place prior to the start of the study and sought input on the study design, procedures and participant-facing documentation. The second will take place after data collection and analysis is complete and will seek input on dissemination materials.

This project also has a steering committee which includes two members of the public (one is a former Active Together patient who has experience of the pathway) as well as academics and clinicians with expertise in cancer and prehabilitation. The steering group will convene twice a year to review study progress and ensure the study is conducted—and the data are generated, documented and reported—in accordance with the protocol, good clinical practice and the applicable regulatory requirements.

### Statistics and analysis

Directed acyclic graphs have been created for the outcome measures in this study to identify confounding factors and determine which variables to adjust for during analysis. Figure 2 shows the causal pathway and potential confounders for investigating the effect of body composition changes on surgical outcomes. Online supplemental material 3 includes directed acyclic graphs for preoperative well-being, post-treatment well-being and 1-year survival. All quantitative data will be treated as continuous data, excluding Clavien-Dindo classification of postoperative surgical complications (ordinal) and the surgical approach, type of surgical complications and treatment pathway (nominal).

**Figure 2 F2:**
[figure not shown]
Directed acyclic graph for investigating the effect of body composition changes on surgical outcomes. Baseline and preoperative well-being include nutritional status, psychological well-being and physical fitness.

Pearson (or Spearman, depending on the distribution of the data) correlation coefficients will be calculated to explore associations between outcome measures (eg, body weight, size and shape, body composition, body mass change, PG-SGA-SF, EQ-5D-5L, etc) and clinical outcomes (eg, surgical complications, length of stay, number of emergency readmissions and length of operating time). P values <0.05 will be considered statistically significant. Linear and multivariate regression models will then be used to investigate the strength of associations between preoperative changes in patient body measures (eg, body weight and composition), self-reported outcomes (ie, questionnaire data) and clinical outcomes. Additionally, exploratory analyses comparing outcomes between groups of participants (eg, those that lose weight vs those that do not) will be completed, with groups created using thresholds used in the previous literature^10^ and/or data-driven approaches such as a median split^11^ or optimal cut-point determination^32^.

Separate linear regression models will be created to investigate the amount of variation in self-reported and clinical outcomes which are explained by preoperative changes in patient body measures. Then, multivariate regression models will be created which combine patient outcome measures that contribute significantly to the estimation of clinical outcomes. Ordinal logistic regression models will also be used to explore the relationship between patient outcome measures and ordinal clinical outcome variables, such as surgical complications (Clavien-Dindo classification) and the surgical approach used. Where the distribution of data indicates it would be appropriate (ie, for non-linear relationships between predictor and outcome variables), other regression approaches such as restricted cubic splines or generalised additive models will be used. Regression analyses are appropriate as this is exploratory research, and this approach allows the observation of relationships between all variables. The regression models will all be adjusted for the variability in time between the assessment points, tumour group and pretreatment therapies where these are shown to reduce residual variance and not introduce collinearity to the model. Any outliers will be investigated to ensure that they are legitimate observations; only implausible data will be removed.

Multiple regression models will be assessed for multicollinearity between input variables using variance inflation factor and tolerance collinearity statistics and for independence of errors using the Durbin-Watson test statistic. If the largest variance inflation factor value is >10, or tolerance values are below 0.2 this could indicate potential issues in the model associated with multicollinearity. Also, if Durbin-Watson values differed significantly from two this would suggest dependence of errors between input variables in the model. Additionally, regression assumptions (eg, homoscedasticity, normally distributed errors) will be checked via diagnostic plots, and transformations of variables will be used if assumptions are not met.

Data from the Active Together service shows that many patients are unable to attend assessment appointments prior to surgery, often due to short notice of surgery dates. This might lead to missing data at the presurgery assessment point (visit 2). All efforts will be made to make attending appointments as convenient as possible for patients. Additionally, patients are routinely weighed before surgery; therefore, the key outcomes of body mass change and surgical outcomes should always be available. Therefore, statistical analyses for body mass change will include all participants, and analyses including body composition, size and shape, and questionnaire data will be performed on a smaller cohort if some data are missing.

Complete case analyses will be performed when covariates (eg, body composition variables) contain missing data. Complete case analysis can lead to biased parameter estimates in regression models if the data are not missing completely at random (MCAR). Therefore, graphical techniques and Little’s hypothesis test of the MCAR assumption will be used to explore whether the MCAR assumption is a reasonable one to make with the collected data. If not, a standard multiple imputation method will be implemented (eg, Multiple Imputation by Chained Equations, Linear Regression Imputation or Predictive Mean Matching).

For linear regression analyses, assuming a medium effect size (F^2^=0.15), significance level=0.05, power=0.8 and number of predictors=6, a sample size of 98 is required.^33^ For correlation, assuming a two-tailed test, a medium effect size (rho=0.3), significance level=0.05 and power=0.8, a sample size of 84 is required.^33^ Therefore, a sample size of 100 participants is required to detect medium effect sizes with acceptable statistical power. Furthermore, 100 participants is a reasonable estimate of the number of potential participants within the study’s time frame based on the demographics of current and previous Active Together patients (ie, number of patients awaiting surgery for upper GI or colorectal cancer with a BMI ≥30 kg/m^2^).

For the data collected through the weight loss intention, strategies and advice questionnaire, the number and proportion of responses for each question will be recorded and subgroup analyses performed depending on the responses, for example comparisons of surgical outcomes between those who lost weight intentionally, those who lost weight unintentionally and those who didn’t lose weight. The final question will be analysed using thematic analysis by manually identifying patterns and themes in the responses and will be reported narratively. Member checking will be undertaken by an independent qualitative researcher to check that the analysis is accurate and has not over-represented or under-represented any aspects of the data.

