#### Secondary data

In addition to the outcomes detailed above that will be gathered by the research team, data will be collected as part of the participants’ usual care from two other sources: from their NHS records for surgical information, hospital length of stay, readmissions and 1-year survival, and from the Active Together service for physical fitness and questionnaire assessments (table 1). These outcomes will be measured at the time points outlined in figure 1. The physical fitness outcomes from Active Together will be collected by members of the Active Together team, with the procedures used to collect this data provided in online supplemental material 2.

**Table 1 T1:** Data collected by the hospital and Active Together.

Hospital data	Active Together outcomes	
Surgical outcomes	Physical fitness	Questionnaires
Clavien-Dindo classification of postoperative surgical complications	6-minute walk test distance (m)	Patient-Generated Subjective Global Assessment Short Form
Type of surgical complications	60-second sit-to-stand repetitions	Quality of life: EuroQol 5-Dimensions 5-Levels
Length of operation time	2-minute step test repetitions	Fatigue: Functional Assessment of Chronic Illness Therapy-Fatigue
Surgical approach	Handgrip strength (kg)	Anxiety: General Anxiety Disorder 7
Length of critical care stay post-surgery	Blood pressure (mm Hg)	Depression: Patient Health Questionnaire 9
Length of hospital stay post-surgery	Physical activity level (exercise vital signs)	Self-Efficacy for Exercise Scale
Readmissions within 30 and 90 days (and reason for this)		
1-year survival		
Treatment pathway		

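### Length of stay, critical care stay and readmissions are analysed on a plain continuous scale with no place for death, so an early postoperative death enters as a short stay with no readmissions

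*Protocol article*

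**What the plan says.** Table 1 (Secondary data) lists "Length of hospital stay post-surgery", critical care stay and "Readmissions within 30 and 90 days (and reason for this" as hospital data. Death appears only as a separate item, "1-year survival".

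Statistics and analysis then sets the scale: "All quantitative data will be treated as continuous data". The exceptions are the Clavien-Dindo grade, surgical approach, type of complication and treatment pathway. Neither of the two stays nor the readmission count is among them.

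The first analysis is stated as "Pearson (or Spearman, depending on the distribution of the data) correlation coefficients will be calculated to explore associations" between the patient measures and "clinical outcomes (eg, surgical complications, length of stay, number of emergency readmissions and length of operating time". Regression follows: "Separate linear regression models will be created to investigate the amount of variation in self-reported and clinical outcomes".

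The same section removes outliers only if they are implausible, keeps every participant in the body mass change analyses, and expects surgical outcomes to be available for everyone. Its missing-data rules deal with missed visits and incomplete covariates.

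**The concern.** A hospital stay can end in two ways, discharge or death, and the number of days does not show which. A readmission count of zero can likewise mean that the patient stayed well at home, or that the patient died and could not be readmitted. On a plain numerical scale the worst result then looks like a good one.

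This would be random noise if deaths were unrelated to the exposure. The Introduction gives reason to think otherwise: it argues that preoperative weight loss may include muscle, and that loss of muscle is probably harmful for morbidity and mortality. If so, the patients with the most harmful change are more likely to be scored as short stays, and the estimated association moves towards no harm. The Introduction also cites earlier findings of no increase in length of stay as reassurance about weight loss, so a weak length-of-stay association here could be read in the same way.

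**Working it through.** **Step 1. The plan's own figures.** These concern sample size and do not depend on how death is scored.
- Regression: noncentral F test with 6 predictors and f² = 0.15. At N = 98, λ = 0.15 × 98 = 14.7 with 6 and 91 degrees of freedom, giving power 0.804. The stated 98 is reproduced.
- Correlation: Fisher z gives ((1.96 + 0.842) / atanh(0.3))² + 3 = 84.9, so 85 against the stated 84. The difference of one is within approximation error.

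**Step 2. The stated rules applied to one patient.** Take a death on day 2 after surgery.
- Scale: continuous, so the stay is 2 days and the readmission count is 0.
- Outlier rule: the value is genuine, so it is kept.
- Population: body mass change analyses include all participants, so the patient is included.
- Missing data: nothing is missing, so no rule applies.

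With an assumed log-normal stay (median 8 days, log-SD 0.6), the share of stays under 2 days is Φ(ln(2/8)/0.6) = Φ(−2.31) = 1%, and under 4 days Φ(ln(4/8)/0.6) = Φ(−1.16) = 12%. A death in the first days is therefore ranked among the shortest stays.

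**Step 3. Chance that this arises.** The article gives no mortality figure. With 100 patients, the chance of at least one early death is 1 − (1 − q)^100. For assumed q of 1%, 2%, 3% and 5% this is 63%, 87%, 95% and 99%.

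**Step 4. Effect on the length-of-stay correlation.** Simulation, n = 100, true correlation 0.3 between a harmful exposure and latent severity, log-normal stay with log-SD 0.6, Spearman test at two-sided 0.05, death scored by its observed stay. Every input except n, the correlation and alpha is an assumption. Entries are mean correlation and power.

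| Assumed deaths | Median stay | None | 2 deaths | 3 deaths | 5 deaths |
|---|---|---|---|---|---|
| The most severe cases, days 1–7 | 7 | 0.289, 84% | 0.254, 73% | 0.236, 66% | 0.215, 58% |
| The most severe cases, days 1–30 | 7 | 0.289, 84% | 0.275, 80% | 0.273, 79% | 0.268, 78% |
| Weighted by severity, days 1–30 | 7 | 0.289, 84% | 0.279, 82% | 0.276, 80% | 0.269, 78% |
| Weighted by severity, days 1–4 | 8 | 0.285, 83% | 0.268, 78% | 0.255, 73% | 0.238, 67% |

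The extreme case loses 84 − 58 = 26 power points. A separate run of that case gave 83 − 60 = 23, hence about 25. With 2 deaths spread over days 1–30 the loss is 84 − 82 = 2 to 84 − 80 = 4 points.

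**Step 5. Effect of ranking death worst.** In the setting of the last row, the results become 0.282 (82%), 0.276 (81%) and 0.271 (79%) for 2, 3 and 5 deaths, so most of the loss is recovered. Where deaths are only weighted by severity and spread over days 1–30, there is little to recover and ranking changes little.

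**Step 6. Readmissions.** With an assumed mean of 0.15 readmissions, about exp(−0.15) = 86% of patients have none. The mean correlation goes from 0.147 with no deaths to 0.138 with 5 and 0.133 with 8. With death ranked worst it is 0.148 and 0.149.

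**The case against.** The strongest objection is that the article states no rule for deaths at all. The continuous scale is a statement about measurement, the sentence on including all participants answers missed second visits, and the outlier rule was written for data errors. Handling of death could sit in an analysis plan that is not shown. This is fair as to intent, and such a plan may contain a rule. However, the point does not rest on silence alone: the article does fix scale, methods, population and exclusions, and applied together they score an early death as described.

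A second objection is that survival and graded complications are analysed in their own right, that length of stay is one example in a list, and that the work is called exploratory. That lowers the stakes: length of stay would be reported beside complications and survival. It does not correct the length-of-stay or readmission coefficients.

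The third objection, on size, largely stands. The large loss of power needs several deaths, all among the most severe cases and all within the first week. A patient who dies after a long complicated stay already has a long stay, so only early deaths mislead on that outcome.

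A reader might also infer that the two outcomes trade off, because a long stay would leave few days at risk within a 30-day window. That holds only if the window runs from surgery, and the article does not state its origin.

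**Conclusion.** The point holds as a cheap improvement to the analysis wording. Under the stated rules an early postoperative death counts as a short stay with no readmissions. If the deaths are related to the exposure, as the Introduction gives reason to expect, the bias is towards no harm.

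Its size is unknown, because the documents give no mortality, timing or stay figures. Under the assumptions shown, the loss for length of stay runs from negligible with 1 or 2 deaths spread over days 1 to 30 to about 25 power points in the extreme case of 5 very early deaths among the most severe patients. The simulations cover Spearman correlation only; Pearson correlation and linear regression were not simulated.

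Three stronger readings are not supported. A fall to about 60% power is not the expected result but the far end of the range. An early death is not one of the best results on both outcomes: on readmissions it probably ties with the majority at zero. Nor do the documents require a change of main outcome: they name no main measure of hospital use, so making days alive and out of hospital the principal one would be a design preference.

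**What to change.** Add a short rule to Statistics and analysis and fix it before outcomes are seen:

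- **Length of stay and critical care stay:** rank in-hospital deaths as the worst value and use a rank-based or ordinal analysis. Spearman correlation and ordinal logistic regression are already in the plan.
- **Readmissions:** analyse among patients discharged alive, count the 30- and 90-day windows from discharge, and report deaths within each window alongside.
- **Sensitivity outcome (optional):** days alive and out of hospital to day 90 after surgery.

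No extra visits or patients are needed. The rule uses discharge and death dates and discharge status; these should be available from the NHS records that already supply stay, readmissions and survival, but the data extraction should be checked to include them. The main cost is interpretive: the length-of-stay result is no longer a mean difference in days, so stays among patients discharged alive should also be described. Restricting readmissions to patients discharged alive selects on survival, which is why the deaths must be shown next to them.

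### The plan permits outcome-driven cut-points and significance-screened predictors on the same 100 participants, with p<0.05 as the only stated criterion and no allowance for the selection

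*Protocol article*

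**What the plan says.** All of this stands in the protocol article under Statistics and analysis.

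- **Criterion.** After the correlations the article states: "P values <0.05 will be considered statistically significant". It gives no other criterion.
- **Group comparisons.** It then announces that "exploratory analyses comparing outcomes between groups of participants (eg, those that lose weight vs those that do not) will be completed".
- **How the groups are formed.** Three routes are open, alone or together. One is a published threshold. The article also names "data-driven approaches such as a median split". As a third route it names "optimal cut-point determination". It does not say which route takes precedence, what range is searched, what is optimised or how the resulting p-value is obtained.
- **Predictor selection.** Separate regressions come first. In the next step, "multivariate regression models will be created which combine patient outcome measures that contribute significantly to the estimation of clinical outcomes".
- **Status.** The article justifies the approach this way: "Regression analyses are appropriate as this is exploratory research".

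The same section also says that directed acyclic graphs settle the choice of adjustment variables, that quantitative data are handled as continuous apart from a few named ordinal and nominal variables, and that splines or generalised additive models are available for non-linear relationships.

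**The concern.** An optimal cut-point is the split at which the outcome difference looks largest. Testing that difference as if the split had been fixed beforehand ignores the search, so the p-value is too small and the effect too large. Screening has the same fault in another form: measures enter the multivariable model because they were significant in these data, and their significance there is then read as evidence.

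The stakes are practical. The Introduction cites a feasibility trial in which patients losing more than 3.2% of body weight had half the surgical complications; the article cites that same trial for the median split. The Introduction also says that better understanding would support recommendations for dietitians and exercise professionals, and warns that weight loss before surgery may do harm through loss of muscle. A chance threshold from 100 participants could be read as advice.

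**Working it through.** **1. The plan's own figures.** The article gives N=98 for regression (f²=0.15, 6 predictors, alpha 0.05, power 0.8) and N=84 for correlation (rho=0.3, two-tailed).
- Regression: noncentral F with 6 and N−7 degrees of freedom and noncentrality 0.15·N. Power is 0.798 at N=97 and 0.804 at N=98, so 98 is reproduced.
- Correlation: Fisher z gives ((1.960+0.842)/atanh 0.3)² + 3 = 84.9, so 85; a noncentral-t version gives 82. The stated 84 is within two of both.

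The target of 100 is therefore taken as given. The article states no error rate for the cut-point analyses.

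**2. Optimal cut-point under the null.** Inputs from the article: N=100 and a two-sided 0.05 criterion. *Assumptions, because the article is silent:* the search range, and a criterion that maximises |t|. Simulation with no association, 60,000 replicates, one continuous outcome; the largest |t| over all allowed cuts is compared with the ordinary critical value.

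| Trimmed at each end | Part searched | Significant at 0.05 | Nominal p needed for a true 5% |
|---|---|---|---|
| 5% | inner 90% | 47% | 0.0028 |
| 10% | inner 80% | 40% | 0.0035 |
| 15% | inner 70% | 35% | 0.0043 |
| 20% | inner 60% | 30% | 0.0052 |
| 25% | inner 50% | 26% | 0.0064 |
| 30% | inner 40% | 23% | 0.0080 |
| 40% | inner 20% | 15% | 0.0144 |

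A binary outcome (30% event rate, assumed) gives 42% for the inner 80% and 31% for the inner 60%; event rates of 20% and 40% are similar. Coarser searches inflate less: 12.5% for the best of three quartile cuts and 25% for the best of nine decile cuts.

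**3. Median split.** The split depends only on the predictor, so for a single outcome the error is preserved: 5.0% simulated. Its cost is power. Splitting a normal predictor at its median multiplies the correlation by √(2/π)=0.798, so 0.30 becomes 0.239. At N=100, power falls from about 86-87% to 68% (simulated; Fisher z gives 86% and 67%).

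**4. Significance screening.** The chance that at least one of m independent null candidates passes at 0.05 is 1−0.95^m. Simulation at N=100 (4,000 replicates), refitting the selected measures jointly, gives the chance that at least one is still significant in the final model.

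| m (assumed) | 1−0.95^m | Still significant after refit |
|---|---|---|
| 3 | 14.3% | 14.5% |
| 5 | 22.6% | 23.2% |
| 8 | 33.7% | 33.0% |

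Refitting therefore gives almost no protection.

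**5. Against the plan's own principles.** Measures in a combined model adjust for one another, so choosing them by significance lets the data set the adjustment, although the article says the directed acyclic graphs do so. Dichotomising weight change likewise departs from the statement that quantitative data are treated as continuous.

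**The case against.** The strongest reply has four parts.

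- **The work is labelled exploratory, and the 0.05 sentence sits with the correlations.** Both are true. The label does not make a maximally selected p-value valid, however, and no other criterion is offered for the later comparisons.
- **The optimal cut-point is one and/or option, and a correction could lie in the cited method or in an analysis plan not shown.** This stands as a limit. A reader might infer that the study will declare a chance threshold; the article shows only that its wording permits it. What the article does fix is an open choice among three kinds of threshold on the same data.
- **The error rate depends on a search range that the article does not give.** This stands too, which is why a range is shown. The lowest value in the table, 15%, is still three times nominal.
- **Much of the remedy is already there:** continuous treatment, splines, directed acyclic graphs, literature thresholds. Correct, and it makes the change cheap. But the article also commits to screening and allows the data-driven groupings alongside.

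Two stronger readings are not supported. A reader might infer that median splits, optimal cut-points and screened predictors all produce chance findings in about a third of null cases. That is wrong for the median split (5%), and screening reaches that level only with about eight independent null candidates. A reader might also add a family-wise rate across all correlations. The article names six example measures and four example outcomes; 6×4=24 tests would give 1−0.95^24=71%, but these are only examples, the measures are plainly correlated, and whether exploratory work needs such control is debatable.

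**Conclusion.** The concern holds for two procedures. First, an optimal cut-point compared at unadjusted 0.05 has a null false-positive rate of about 30-40% for a search over the inner 60-80% of the data, and 15-47% over the ranges assumed here, given N=100, one outcome and a maximised test statistic. Second, selecting predictors by significance in the same data lets in at least one false predictor in about 15%, 23% or a third of null cases with 3, 5 or 8 independent candidates; correlated candidates would change these figures. The median split is a problem of efficiency and of a sample-dependent threshold, not of type I error. The point should be settled before analysis, but it does not undermine the continuous regressions as such.

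**What to change.** - Base inference on continuous change in body mass and composition, using the splines already planned where relationships are non-linear.
- Form groups for inference only at a literature threshold named before the data are seen.
- Drop the median split as an inferential analysis.
- Show any optimal cut-point as descriptive only, or with a maximally selected or permutation p-value and a bootstrap-corrected effect. State the search range and criterion.
- Replace significance screening with prespecified exposure models adjusted for the covariates that the directed acyclic graphs identify.

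The cost is some rewording and a little extra programming if a corrected cut-point is kept. The downside is fewer nominally significant exploratory results. No further data or participants are needed.

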**Ethics and dissemination:**

Ethical approval has been obtained from the Health Research Authority (Integrated Research Application System project ID 361634; Research Ethics Comittee reference 26/YH/0019). Written informed consent will be obtained from all participants. Data will be processed in accordance with General Data Protection Regulations and the Data Protection Act 2018. Findings will be disseminated via peer-reviewed publications, conference presentations and patient and public involvement activities.

STRENGTHS AND LIMITATIONS OF THIS STUDYThe observational nature of the study provides an ecologically valid insight into patient outcomes in an evidence-based cancer prehabilitation service.Longitudinal assessment of body mass and composition, surgical outcomes, physical fitness, nutritional status and quality of life allow investigation of the relationships between the changes in each metric across the perioperative period.The observational nature of the study precludes the ability to draw causal inferences.The potential heterogeneity of participant characteristics and treatment pathway may confound the associations reported; however, these will be accounted for statistically where possible.

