**Figure 1 F1:**
[figure not shown]
Schematic of data collection in relation to study-specific visits, surgery, and the Active Together assessment pathway. Data will be collected by the Active Together service at baseline, pretreatment and post-treatment, and at 90 days post treatment. Active Together define treatment to include additional forms of acute treatment, for example chemo or radiotherapy, and so pretreatment and post-treatment assessments may occur at varying intervals from surgery. Study-specific data will be collected twice: once as soon as possible after diagnosis, and once within the 2 weeks prior to surgery. Due to differences in treatment pathways and surgery waiting times, the duration between visit 1 and visit 2 will vary between participants, as well as the duration between Active Together assessments. Surgical data will be collected from the surgical team after patient discharge. The study specific, surgical and Active Together outcomes are outlined in the Procedures section.

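### Fitness and questionnaire outcomes are recorded at both post-treatment and 90 days, but no planned model uses repeated values within a patient; a mixed model would add modest precision and protect against selective 90-day attendance

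*Protocol article*

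**What the plan says.** The Figure 1 legend (Study design) gives the service's schedule: "Data will be collected by the Active Together service at baseline, pretreatment and post-treatment, and at 90 days post treatment". Procedures, Secondary data, ties the hospital and service outcomes in Table 1 to that schedule: "These outcomes will be measured at the time points outlined in figure 1". The service's share of Table 1 includes walk distance, sit-to-stand, step test, grip strength, PG-SGA-SF, EQ-5D-5L, fatigue, anxiety, depression and exercise self-efficacy. The legend adds that "pretreatment and post-treatment assessments may occur at varying intervals from surgery".

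Statistics and analysis begins with correlations and then lists the models:
- "Separate linear regression models will be created to investigate the amount of variation in self-reported and clinical outcomes which are explained by preoperative changes"
- "multivariate regression models will be created which combine patient outcome measures that contribute significantly to the estimation of clinical outcomes"
- proportional-odds type (ordinal logistic) models for graded results such as the Clavien-Dindo class
- restricted cubic splines or generalised additive models where relationships are non-linear.

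Time between assessments enters only as an adjuster, kept if it reduces residual variance without causing collinearity. On missing data, questionnaire and body-composition analyses use a smaller cohort. The complete-case rule is stated for missing covariates, with multiple imputation if the data do not look missing completely at random. Body mass change is expected for every participant, because patients are routinely weighed before surgery.

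**The concern.** Two of the assessments, post-treatment and 90 days, fall after the preoperative body change that is the exposure. For each outcome, most patients should therefore have two correlated values that could both inform the association. None of the named models has a within-patient term, and the Durbin-Watson check does not supply one.

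If each assessment is regressed separately, a patient who misses the 90-day visit contributes nothing to the 90-day estimate, although the post-treatment value says something about the missing one. Two things are at stake. The first is some precision, in a study of 100 with only 2 patients above the 98 that its regression calculation requires. The second is bias: if people doing badly after treatment are less likely to return at 90 days, those who do return are a selected group.

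The article itself foresees patients with the earlier value but not the later one. Under Ethics and dissemination, someone who withdraws after surgery keeps the data already collected but contributes nothing further.

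**Working it through.** **1. The plan's own figures.** These reproduce.
- Regression: overall F test with 6 predictors, f² = 0.15, noncentrality 0.15·N and N − 7 error degrees of freedom. Power first reaches 0.80 at N = 98 (0.804).
- Correlation: ρ = 0.3, Fisher z with the bias term. N = 84 (85 without the bias term).

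The sample-size section is not in error.

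**2. Inputs the article does not give.** Neither the share of missing outcomes (m) nor the within-patient residual correlation (r) is stated. I assume m = 0, 25% or 40% independently at each of the two assessments, and r = 0.6 with a range of 0.4 to 0.8. The true correlation with body change is 0.3, the article's medium effect, at both assessments, with n = 100.

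**3. Like-for-like precision: the slope at one assessment, estimated alone or jointly.**

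Patients with both values: a = n(1 − m)². Patients with only one given value: b = n·m(1 − m). Put I = a/(1 − r²) + b and J = r·a/(1 − r²). The effective number for one time-specific slope is n_eff = I − J²/I. Analysed alone it is n(1 − m). Approximate power = Φ(atanh(0.3)·√(n_eff − 3) − 1.96), with atanh(0.3) = 0.3095.

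For r = 0.6:
- m = 0: I = 156.25, J = 93.75, n_eff = 156.25 − 56.25 = 100. Power is 0.86 either way, so there is no gain.
- m = 25%: a = 56.25, b = 18.75, I = 87.89 + 18.75 = 106.64, J = 52.73, n_eff = 106.64 − 26.08 = 80.6 against 75. Power 0.78 against 0.75.
- m = 40%: a = 36, b = 24, I = 56.25 + 24 = 80.25, J = 33.75, n_eff = 80.25 − 14.19 = 66.1 against 60. Power 0.69 against 0.65.

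Range over r, same formula: at 25% missing, n_eff is 77.3 (r = 0.4) to 85.7 (r = 0.8), power 0.76 to 0.80. At 40% it is 62.5 to 72.4, power 0.67 to 0.73.

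Simulation at r = 0.6 agrees: 75-77% alone against 78-79% jointly at 25% missing, and 67% against 71-72% at 40%.

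**4. Missing exposure instead of missing outcome.** With 25% of exposures missing, simulated power is 76% for both methods; with 40%, 66% for both. A mixed model cannot use a patient whose body change is unknown.

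**5. Selective attendance.** With 90-day attendance made to depend on the post-treatment value and a true slope of 0.30, the separate 90-day regression averaged 0.26 and the joint model 0.30. The bias shrinks as that dependence weakens and disappears when attendance is unrelated to earlier status.

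**6. Average slope.** If the association is 0.3 at one assessment and 0.1 at the other, with 25% missing, the average slope has about 55% power against 74% for regression at the stronger assessment. If the second association is zero and data are complete, it is 39% against 87%.

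**The case against.** The strongest reply is that this is a condensed article. It never says which assessment enters which model, and the quoted sentence speaks of self-reported and clinical outcomes rather than fitness tests. Analysing each assessment alone is therefore an inference. Baseline well-being is in the causal graph and may be adjusted for, and multiple imputation, if triggered, could draw on other assessments. All of that stands, so one cannot say that within-patient information is certain to be discarded. What remains is that the article states and defends a specific family of models, and none of them links post-treatment with 90-day values.

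A second reply also stands in part. The missed appointments the article expects are before surgery, which for body composition means a missing exposure, and step 4 shows no gain there. But body mass change is expected for everyone, so for that exposure outcome attendance is what limits the analysis. The complete-case rule and its imputation fallback are written for covariates and do not clearly cover a missing outcome.

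Three stronger readings are tempting and not supported:
- **A power gain of 13 to 21 points.** This appears only when a single-time slope is compared with a common slope assumed equal at both assessments. That changes the estimand, and nothing in the article supports equality.
- **Inflated false positives from stacking assessments as independent rows.** The article does not propose that analysis. Nor does the mixed model remove the two tests per outcome, since it also reports two time-specific slopes.
- **That the longitudinal aim goes unanswered.** The strengths list says "Longitudinal assessment of body mass and composition, surgical outcomes, physical fitness, nutritional status and quality of life allow investigation of the relationships" between changes in the metrics. Change-score correlations and regressions can address that.

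**Conclusion.** The point holds as a moderate improvement and does not invalidate the plan. Separate regressions per assessment are valid if absences are completely at random, and the loss is then small: about 2 to 5 points of power for the same slope at an assumed 25-40% missing and residual correlation 0.6, and nothing with complete outcomes or when only the exposure is missing. The better reason to change is bias. When 90-day attendance depends on the post-treatment value, the joint model is valid under missing at random given the observed values, whereas the separate 90-day regression is not. The 0.26 against 0.30 is one simulated case. The real size depends on attendance rates and on how strongly attendance follows earlier status, and the article gives neither.

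**What to change.** For each outcome recorded at both post-treatment and 90 days, state one linear mixed model containing:
- time, either as assessment (with an unstructured covariance) or as actual days since surgery (with a patient random intercept), the latter suiting the irregular spacing the article describes;
- the body-change exposure and its interaction with time;
- the planned adjusters.

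Report the time-specific slopes as the main estimates. If days are used, evaluate the slopes at stated days. Give the average slope only as a secondary summary, because it loses power when the association differs over time. Add a sentence saying that patients with either outcome value are included, so that the handling of missing outcomes is explicit alongside the covariate rule. Keep single-record regression for outcomes recorded once, such as operating time and length of stay.

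The cost is a paragraph of wording and a little more analysis work. No extra patients, visits or data are needed.
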